## Abstract

**Background:**

Although care pathways are often said to promote teamwork, high-level evidence that supports this statement is lacking. Furthermore, knowledge on conditions and facilitators for successful pathway implementation is scarce. The objective of the European Quality of Care Pathway (EQCP) study is therefore to study the impact of care pathways on interprofessional teamwork and to build up understanding on the implementation process.

**Methods/design:**

An international post-test-only cluster Randomised Controlled Trial (cRCT), combined with process evaluations, will be performed in Belgium, Ireland, Italy, and Portugal. Teams caring for proximal femur fracture (PFF) patients and patients hospitalized with an exacerbation of chronic obstructive pulmonary disease (COPD) will be randomised into an intervention and control group. The intervention group will implement a care pathway for PFF or COPD containing three active components: a formative evaluation of the actual teams’ performance, a set of evidence-based key interventions, and a training in care pathway-development. The control group will provide usual care. A set of team input, process and output indicators will be used as effect measures. The main outcome indicator will be relational coordination. Next to these, process measures during and after pathway development will be used to evaluate the implementation processes. In total, 132 teams have agreed to participate, of which 68 were randomly assigned to the intervention group and 64 to the control group. Based on power analysis, a sample of 475 team members per arm is required. To analyze results, multilevel analysis will be performed.

**Discussion:**

Results from our study will enhance understanding on the active components of care pathways. Through this, preferred implementation strategies can be defined.

**Trail registration:**

NCT01435538

## Background

Interprofessional teamwork is essential for the delivery of high quality healthcare. The report of the Institute of Medicine (IOM) *‘To Err is Human: Building a Safer Health System’* showed that 3% to 4% of patients hospitalized in the United States (US) were harmed by the care they received. The IOM concluded that poor teamwork and communication was a contributing factor in more than one-half of medical errors [1,2]. Classen *et al.* indicate that adverse events rates may be even ten times higher than previously measured [3]. Teamwork in healthcare is defined as a dynamic process involving two or more health professionals with complementary backgrounds and skills, sharing common health goals, and exercising concerted physical and mental effort in assessing, planning, or evaluating patient care [4]. In industries such as aviation and automobile manufacturing, the value of high-performance teams has long been realized [5]. The Agency for Healthcare and Research Quality (AHRQ) has argued to learn from the experience in these industries and implement various interventions that could improve teamwork as a strategy for enhancing patient safety and reducing medical errors [6]. A meta-analysis on team-training interventions across different settings reported that they account for approximately 20% of the variance in team performance [7]. A RAND report that reviewed 16 healthcare studies found empirical evidence supporting the relationship between teamwork and patient outcomes [8].

One of the interventions that can promote teamwork in healthcare is the implementation of care pathways [9-12]. Care pathways are widely used quality improvement initiatives for organising and reorganising care processes [13]. Compared with other care coordination interventions, such as the chronic care model or integrated care, care pathways are most effective for standardizing low complexity and low uncertainty care processes [14]. Uncertainty implies in the context of care coordination that the course of disease or treatment of a particular patient is unpredictable. The use of care pathways supports healthcare teams in implementing evidence-based key interventions and reduce clinical variations in everyday practice [15]. Furthermore, they are high-performing work systems that improve organisational performance by strengthening relationships and coordination among team members [10,11]. Considering different types of team training, as defined by the AHRQ [6], we see care pathway development as a behaviour change intervention containing a mix of cross-training, self-correction, and team-building exercises. Through care pathway development, roles and tasks of team members are traded, interprofessional relations are improved, feedback on performance is provided, short- and long-term team goals are set, evidence-based practice increases, an overall team vision and shared mental model is built up, and high-performance teams can be established.

Looking at most systematic reviews on pathway-effectiveness studies, the primarily focus is on how they affect hospital costs, patient outcomes, and length of stay [16-18]. The way they affect teamwork is seldom documented. This could be explained because the main goal of care pathways is in fact to improve patient processes and outcomes. Improved teamwork is then merely seen as one of the important mediators and facilitators to achieve that goal [19,20]. However, as Thomas *et al.* state, quality improvement initiatives as care pathways, although not always explicitly targeted, could actually improve teamwork and even have better results for patients than other team training interventions that focus solely on teamwork [21]. A recent systematic review did find a positive, but cautious, indication that a relationship between care pathways and teamwork does exist [12]. Although evidence was of rather low quality, most frequently positive effects of care pathways were found on staff knowledge, interprofessional documentation, team communication, and team relations. The review also identified some negative effects of care pathways, of which most importantly were increased workload and emerging team conflicts through care pathway implementation. Furthermore, as mentioned in their commentary on the review by Salas *et al.*, good teamwork is not only about standardized communication protocols [22]. Attention in care pathways should be given to create the ability to adapt, innovate, and react efficiently and effectively when the situation calls for it. The review concluded that the absence of high-level evidence is due to the lack of high-quality designs and the failure to use validated team indicators in pathway-effectiveness studies.

The European Pathway Association (E-P-A) defines a care pathway as ‘a *complex intervention* for the mutual decision making and organisation of care for a well-defined group of patients during a well-defined period’ [23]. As complex interventions, they are built up from a number of components that may act both independently and interdependently [24]. Although they are difficult to specify, these interacting components seem essential to the proper functioning of the intervention. The more it is difficult to exactly define the active components of an intervention, and how these interrelate, the more it is likely that the intervention is a complex one [24,25]. Care pathways seem to be at the higher end of the complexity spectrum. According to an international survey on use of care pathways, possible active components are increased evidence-based care, improved coordination of the care process, improved communication with the patient, improved teamwork, improved follow-up and increased efficiency [13]. Nonetheless, strong evidence on active components and causal pathways is lacking. Furthermore, knowledge on the process of pathway implementation is sparse and variations in how organisations go about the implementation process are large [19]. Multiple behavioural and organisational components will influence the extent to which they can be successfully integrated into everyday healthcare practice. Evaluating and implementing care pathways therefore requires understanding on how and in what circumstances they work by exploring the context in which they are implemented and the interrelating mechanisms that define their success [26,27].

### Objectives

The primary objective of the European Quality of Care Pathways (EQCP) study is to evaluate the impact of care pathways on interprofessional teamwork in healthcare teams in an acute hospital setting. A secondary goal is to build up knowledge on the active components of care pathways and on the conditions under which they can be most effective through evaluation of the implementation processes.

## Methods

### Setting

The EQCP study is an international multicentre research project launched by the European Pathway Association (E-P-A) (http://www.E-P-A.org), an international not-for-profit association. The E-P-A is collaborating with the Centre for Health Services and Nursing Research of the Faculty of Medicine of the Catholic University Leuven (Belgium) and the School of Public Health of the Amedeo Avogadro University of Eastern Piedmont (Italy) who take the scientific lead in this study. As explained in more detail in Vanhaecht *et al.*[23], the overall project consists of three parts: a trial focusing on the impact of a care pathway for exacerbation of chronic obstructive pulmonary disease (COPD-exacerbation) on patient processes and outcomes; a trial focusing on the impact of a care pathway for proximal femur fracture (PFF) on patient processes and outcomes; and a trial we are discussing here focusing on the impact of care pathways on interprofessional teamwork in which both COPD-exacerbation and PFF-clinical teams are included. The study is being performed in four countries: Belgium, Ireland, Italy and Portugal. In each country, a research centre is coordinating the project based on an international agreed protocol and a national coordinator is appointed. Furthermore, each participating team is asked to appoint a study coordinator as local facilitator for the study.

### Study design

To evaluate the effect of the care pathway, a stratified post-test-only cluster randomised controlled trial (cRCT) is used (Figure 1). In cRCTs, groups of people, rather than individuals, are randomised into an intervention and a control group. Because care pathways are complex interventions and they are developed for and will affect groups of people, a cluster randomised design is required to evaluate their effectiveness [24,25]. Each cluster consists of all individual members of the interprofessional team caring for patients hospitalized for COPD-exacerbation or PFF in a particular hospital. Stratified randomisation was used to assign the teams to an intervention group (using care pathways) and a control group (usual care). Interprofessional teams were randomised. COPD/PFF was used as blocking factor. To ensure that clusters in both arms are in balance, they are stratified for country-level, hospital type (teaching versus non teaching), size of hospitals (<600 and ≥600 beds), and annual volume of patients (<300 and ≥300 patients). Before the start of the randomisation process, random numbers were assigned to each cluster by a researcher not involved in the study, using the online available tool ‘Research Randomizer’ (http://www.randomizer.org). Next, the researcher randomly allocated the coded clusters to the intervention or control group using the same online tool. Through this, the randomisation process itself was fully concealed. Afterward, the research team and the participating teams were notified to which group they were allocated just before the start of the intervention. Each team randomised in the intervention group will implement the complex intervention for the development and implementation of a care pathway for COPD-exacerbation or PFF (see in more detail below). The teams randomised in the control group will not implement the complex intervention, and thus will provide usual care. The intervention teams will have about nine months to implement the complex intervention. After this time period, a summative evaluation will be performed in which performance on team indicators will be compared between the intervention and control group.

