### Measures

The set of effect measures is described in Table 1. Teamwork is traditionally described using systems theory with an ‘input-process-output’ based approach [6]. This implies that effectiveness of teamwork is defined by a complex set of interactions between team inputs (context and structure of the team), team processes, and team outputs. Because we want to study the impact of care pathways on all facets of teamwork, we adopted this multifaceted ‘input-process-output’ approach in our choice of team indicators. The selection of measures is based on the international expert panel on relevant indicators to follow-up in care processes [32] and the systematic review of the relationship between care pathways and teamwork [12]. Hence, the research team made a substantiated decision on the measures based both on identified relevance to follow-up and expected effect of care pathways. As mentioned before, relational coordination is our primary effect measure. Next to the effect measures, a set of covariates will also be measured (Table 2). All team indicators will be analyzed on individual level, except for some team input indicators that will be measured on cluster level. These data will be collected with the use of both validated tools and structured questionnaires developed by the research team. The study coordinators will be trained in how all tools need to be completed. To guarantee anonymity, the team members will be asked to return the completed surveys to the study coordinators in a closed envelope. Afterward, these closed envelopes will be collected by a member of the research team.

**Table 1 T1:** Set of effect measures

**Effect measures**	**Typology**	**Level of analysis**	**Description**	**Instrument**	**Respondents**
Team composition	Team input	Cluster level	The different professional groups of which the team is built up of.	Team membership list	Study coordinator
Team reflexivity	Team input	Cluster level	Frequency of follow up of the care process.	Structured questionnaire	Study coordinator
Team meetings	Team input	Cluster level	Frequency of team meetings.	Structured questionnaire	Study coordinator
			Number of different professional groups attending team meetings.		
Leadership structure	Team input	Cluster level	Leadership structure of the team: No team leader/1 team leader/shared leadership	Structured questionnaire	Study coordinator

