Work Engagement	Team output	Individual level	Level of engagement to work:	Burn Out Inventory[40]	Team members
			- Emotional exhaustion (5 items)		
			- Mental detachment (5 items)		
			- Level of competence (5 items)		

**Table 2 T2:** Set of covariates

**Covariates**	**Level of analysis**	**Description**	**Instrument**	**Respondents**
Randomisation group	Cluster level	Group in which the team was randomised.	Structured questionnaire	Study coordinator
Patient group	Cluster level	Patient group for which the care pathway is being developed.	Structured questionnaire	Study coordinator
Team size	Cluster level	Number of individuals in the team.	Team membership list	Study coordinator
Hospital characteristics	Cluster level	- Number of beds	Structured questionnaire	Study coordinator
		- Patient volume		
		- Teaching status		
		- Dedicated ward or not		
Team tenure	Cluster level	Average number of years that the team members are part of the team.	Structured questionnaire	Team members
Individual characteristics of the team member	Individual level	- Age and gender	Structured questionnaire	Team members
		- Professional group of team member		
		- % of working time		
		- Years of experience with the patient group		
		- Years of being a team member		
		- Has the team member a leading role within the team		

The process measures that will be used in the intervention group are described in Table 3. First, to measure the level of adherence to the complex intervention, the study coordinator will have to score to what extent the evidence-based key interventions were actually implemented. Second, to evaluate the implementation process, process follow-up files will be administered to the study coordinators at several time points during and after implementation. Furthermore, semi-structured interviews with key stakeholders of each cluster will be performed after implementation. We are planning to interview representatives of three groups of stakeholders: the study coordinator, hospital management, and key stakeholders of the interprofessional team. For each of these groups, a specific interview guide will be developed. Considering the large international sample, to enhance feasibility, the interviews will only be performed in a selection of clusters.

**Table 3 T3:** Set of process measures

**Process measures**	**Typology**	**Description**	**Instrument**	**Respondents**

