### Statistical analysis

To analyze results, multilevel analysis will be performed. Common descriptive statistics (Fisher exact and Kruskal Wallis test for categorical and continuous variables, respectively) will be performed on the cluster level. The differences in the effect measures will be evaluated on team or individual level using respectively random-effects logistic or linear regression models, and accounting for the clustering effect. Statistical significance will be defined as a two-sided p-value <0.05. All analyses will be carried out using SAS 9.2 statistical software.

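### The article does not say that the five stratification factors enter the models, and country, one of the five, is missing from the covariate list

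*Protocol article*

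**What the plan says.** The Study design section names five factors that governed allocation. For patient group it says "COPD/PFF was used as blocking factor". For the others it says "To ensure that clusters in both arms are in balance, they are stratified for country-level, hospital type (teaching versus non teaching", followed by "size of hospitals (<600 and ≥600 beds), and annual volume of patients (<300 and ≥300 patients". The Setting section gives country four levels: "The study is being performed in four countries: Belgium, Ireland, Italy and Portugal".

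The only modelling rule is in the Statistical analysis section. Effect measures are compared "using respectively random-effects logistic or linear regression models, and accounting for the clustering effect". No regressor is named there.

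Table 2, headed "Set of covariates", lists randomisation group, patient group, team size, hospital characteristics (beds, volume, teaching status, dedicated ward), team tenure and individual characteristics. Country is not in it. The Measures section introduces the table with "Next to the effect measures, a set of covariates will also be measured (Table 2" and does not say which of these variables enter a model.

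**The concern.** When allocation is stratified on factors that predict the outcome, the true sampling variation of the treatment contrast shrinks. A model that leaves those factors out still counts their variance as noise. Its confidence intervals are then too wide and its test rejects less often than the nominal level.

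Where stratification does not fully achieve balance, leaving the factors out also leaves the remaining imbalance in the estimate. That matters more here than in a trial with a baseline: the design is post-test-only, so there is no pre-intervention relational coordination score in both arms to take up differences between teams. The stratifiers are the main pre-randomisation information at team level.

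The text gives a specific reason for concern beyond brevity. Table 2 is itemised in detail and carries four of the five stratifiers. An analyst who built the model from that list would drop the fifth, country.

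**Working it through.** **1. Setting the sections side by side**

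| Factor | Levels | Used in allocation | In Table 2 | Named in Statistical analysis |
|---|---|---|---|---|
| Patient group (COPD/PFF) | 2 | yes | yes | no |
| Country | 4 | yes | **no** | no |
| Teaching status | 2 | yes | yes | no |
| Beds | 2 | yes | yes | no |
| Annual volume | 2 | yes | yes | no |

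As main effects these cost 1 + 3 + 1 + 1 + 1 = 7 df. If they were fully crossed, which the article does not say, there would be 2 × 4 × 2 × 2 × 2 = 64 cells for 132 teams. That averages 132/64 = 2.06 teams per cell, so balance would not be guaranteed.

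**2. The plan's own sample size**

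For 40% against 30%, two-sided alpha 0.05 and power 80%:

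n = [1.96·√(2·0.35·0.65) + 0.8416·√(0.40·0.60 + 0.30·0.70)]² / 0.10² = 356 per arm, within 3% of the stated 364.

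The stated inflation factor is 1 + 17 × 0.018 = 1.306; 364 × 1.306 = 475; 475/17 = 27.9, so 28 clusters. The figures reproduce. They contain no term for stratification, so they neither support nor refute the point. They do supply the ICC (0.018) and the team size (17) used next.

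**3. Size of the effect on the standard error**

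Let f be the share of between-team variance that the factors explain. The article does not give f, so its full range is shown. With balance on the factors and total variance scaled to 1, the variance of a team mean is:

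- unadjusted: 0.018 + 0.982/17 = 0.0758
- adjusted: 0.018·(1 − f) + 0.982/17

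At f = 0.5 the adjusted value is 0.009 + 0.0578 = 0.0668, so the SE ratio is √(0.0758/0.0668) = 1.065. The true type I error of the unadjusted test is 2·[1 − Φ(1.96 × ratio)]. Power is for a 10-point difference with variance 0.35 × 0.65 and 28 teams per arm.

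| f | SE ratio | Type I error, unadjusted | Power unadjusted | Power adjusted |
|---|---|---|---|---|
| 0 | 1.00 | 0.050 | 81.3% | 81.3% |
| 0.25 | 1.03 | 0.043 | 82.1% | 83.6% |
| 0.5 | 1.065 | 0.037 | 82.8% | 85.9% |
| 0.75 | 1.10 | 0.031 | 83.7% | 88.2% |
| 1 | 1.145 | 0.025 | 84.6% | 90.4% |

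With the 132 teams randomised, taken as 66 per arm, power at f = 0.5 is 99.5% unadjusted and 99.7% adjusted.

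**4. Simulation without perfect balance**

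Team means were simulated for 132 teams allocated within the 64 crossed cells, with assumed distributions of the factors and 4,000 runs, at ICC 0.018 and f = 0.5:

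- unadjusted: mean reported SE 0.0478 against an empirical SD of 0.0461 (ratio 1.04), type I error 0.039
- adjusted for main effects: 0.0452 against 0.0456, type I error 0.048

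The Monte Carlo standard error of these rates is about √(0.039 × 0.961/4000) = 0.003. The simulation agrees with the formula in direction and rough size, and should not be read more finely than that.

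**The case against.** The strongest reply is that the Statistical analysis section names no regressor at all, not even the treatment arm. The arm appears as the first row of Table 2, so Table 2 is naturally read as the list of model terms, and it holds four of the five stratifiers. Choosing which covariates enter which model is commonly left to a full protocol or SAP. This stands for those four: their use is unstated, not excluded. A reader might infer that the analysis leaves out all five factors, but the article does not say so.

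For country the reply is weaker. Table 2 is partly a data-collection table, and country is known for every team without a questionnaire, so its absence does not prove that the model omits it. The mismatch with the Study design section remains all the same.

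A reader might also infer the following, which the article does not support:

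- **That standard errors will be too large.** This holds only if the factors are prognostic, reasonably balanced and omitted. At f = 0 there is no inflation. Excess standard error and uncorrected imbalance also pull against each other: the better the balance, the more the first applies and the less the second. In the simulation the empirical SD was 0.0461 unadjusted and 0.0456 adjusted, so residual imbalance cost only about 1% in precision.
- **That country is the largest source of variation between teams.** The only relational coordination data reported are Belgian, so they show nothing about differences between countries.
- **That the distortion is large.** It would grow with the ICC, but the article states only 0.018.

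Finally, the calculation is for linear models. In random-effects logistic models adjustment also changes the quantity being estimated, and 7 df may be too many for team-level outcomes with at most 132 units.

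**Conclusion.** The point holds as a mismatch within the article and a gap in the analysis rule. Five factors governed allocation, the modelling rule names none of them, and the itemised covariate list leaves out country. The country omission is the firmest part.

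The consequence is conditional and modest. If the factors are omitted and are prognostic, the analysis is conservative and less efficient. At ICC 0.018 and 17 members per team the standard error is 0 to 15% too large. At f = 0.5 it is about 6% too large by formula and about 4% in the simulation, with type I error 0.037 to 0.039. The share f is an assumption throughout. The conservatism does not raise the false-positive rate, and power stays above 80% at the planned 28 clusters per arm. Any residual imbalance on the factors would remain in the estimate, with no baseline score to offset it.

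The change is worth making because it meets both problems at no data cost and settles the choice between adjusted and unadjusted results before the data are seen.

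**What to change.** - Add country to Table 2 as a cluster-level covariate.
- State in the Statistical analysis section that patient group, country, teaching status, bed category and volume category enter the primary relational coordination model as fixed main effects (7 df), alongside the random team effect.
- Apply the same terms to the other individual-level models.
- For team-level logistic models, with at most 132 units, include the factors where the data support it.

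The cost is one table row and a sentence or two. Every factor was needed for randomisation, so its value is already known for each team.
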